**Figure 2. F2:**
[figure not shown]
Locations of acupoints. ST36 = Zusanli, PC6 = Neiguan.

### 3.2. Control group

On the basis of symptomatic treatment drugs, symptomatic treatment will be given for the following symptoms of autonomic nerve dysfunction, and clinical observation was conducted for 1 month: If the heart rate is greater than 100 beats/minutes, take propranolol tablets, and the dose is adjusted according to symptoms; if the Ashworth classification of any limb muscle tone improvement is greater than or equal to 3, take clonazepam tablets, and the dose is adjusted according to symptoms; if infection is excluded, body temperature is above 38°C with sweating symptoms, bromocriptine is administered, and the dose is adjusted according to symptoms.

In addition to symptomatic treatment drugs, other related treatments are prohibited during the observation period. Doctors check the patient’s concomitant medication at each visit, and record the name of the drug (or other therapy name), dosage, frequency and time of use in the study medical record “Concomitant Medication Table” for analysis and reporting when summarizing.

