## Abstract

Stroke patients with autonomic dysfunction are more likely to develop cardiac problems, which have been linked to lower functional outcomes and increased mortality. In this study, heart rate variability (HRV) detection paired with the Clinical Feature Scale will be utilized to elucidate the immediate impact of manual acupuncture on autonomic dysfunction of varying severity in the convalescence stroke phase.

This is a randomized, single-blind, controlled clinical trial approach. At a ratio of 1:1, 60 appropriate patients will be randomly randomized into either the experimental or control group. On the basis of symptomatic treatment drugs, the experimental group will additionally undertake acupuncture therapy 3 times a week for 4 weeks, for a total of 12 times. Primary outcomes include 24-hour HRV and 60-minute HRV detection at week 4 compared with baseline. The secondary outcome is the score of clinical feature scale at week 4 compared with the baseline. Adverse events and safety indices will be recorded throughout the experiment. The SPSS V.25.0 statistical program was applied for analysis, and measurement data were expressed as mean ± SD.

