## 2. Methods

### 2.1. Study design

This randomized, single-blind, controlled clinical trial will be conducted in Longhua Hospital Affiliated to Shanghai University of Traditional Chinese Medicine. A flow diagram of the trial is shown in Figure 1. The schedule of enrollment, interventions and assessments are presented in Table 1.

**Table 1 T1:** The schedule of enrollment, interventions and assessments are presented.

	Sutdy Period					
	Screening	Baseline	Treatment Period (wk)			
Timepoint		*0*	*1*	*2*	*3*	*4*
Enrolment						
Eligibility screen	X					
Informed consent	X					
Allocation		X				
Interventions:						
*Experimental group*			X	X	X	X
*Control group*			X	X	X	X
Assessments:						
*Physical examination*		X				
*Acupuncture Safety and tolerance test*		X				
*Blind method success rate test*		X				
*24-h HRV*		X				X
*60-min HRV*			X	X	X	X
*CFS*		X				X
*Concomitant medication*		X	X	X	X	X
*Adverse reaction record*		X	X	X	X	X

CFS = clinical feature scale, HRV = heart rate variability.

Physical examination include height, weight, blood pressure and heart rate.

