## 3. Interventions

### 3.1. Experimental group

All subjects are able to use basic symptomatic treatment drugs, such as hypotensor, lipid-lowering drugs, hypoglycemic drugs, antiplatelet aggregation drugs, etc.

On the basis of symptomatic treatment drugs, acupuncture will be performed. The patients in the acupuncture group will lie in the prone position. The selected acupoints are Neiguan (PC6), Zusanli (ST36). All acupoints are localized according to the WHO Standard Acupuncture Locations^[18]^ and are exhibited in Table 2 and Figure 2. After accurate positioning and routinely disinfecting the local skin of the patient and the hands of the physician with 75% ethanol, physician will insert sterile disposable acupuncture needles (Hanyi, 0.25 mm × 40 mm) into the selected acupuncture points and apply the manipulation of even reinforcing and reducing movement for 1 minute, the rotating angle is between 60° to 210°, and the depth is 0.5 to 1 cun (1 cun ≈ 20 mm). The needles will be kept for 20 minutes after stimulating the acupuncture points to reach De qi (a compositional sensation including soreness, numbness, distention, and heaviness), which is believed to be an essential component for acupuncture efficacy. Acupuncture will be performed once every other day, 3 times a week, for a total of 12 times.

**Table 2 T2:** Locations and manipulations of acupoints.

Acupoint	Location	Manipulation
Neiguan (PC6)	Between the palmaris longus tendon and the flexor carpi radialis tendon, 2 cun above the transverse stria of the distal carpometacarpus	Puncture perpendicularly to a depth of 0.5–1 cun with even reinforcing and reducing movement for 1 min
Zusanli (ST36)	Three cun directly below Dubi, and 1 finger- breadth lateral to the anterior border of the tibia	Puncture perpendicularly to a depth of 1–2 cun with even reinforcing and reducing movement for 1 min

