### 4.2. Secondary outcomes

The secondary outcome measure is the score change in the Clinical Feature Scale compared with baseline at week 4. With a total score of 0 to 18 points, CFS is used to assess the severity of clinical symptoms of autonomic nerve function. According to heart rate, respiration, blood pressure, body temperature, sweating and posture at the time of seizure, it divides the severity of autonomic nerve dysfunction into 4 grades: normal (0 points), mild (1–6 points), moderate (7–12 points), and severe (≥13 points). All patients will be scored at baseline (week 0) and at the end of treatment (week 4), and the changes in scores before and after treatment will be compared.

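### Symptom-triggered propranolol, clonazepam and bromocriptine are written for the control group only, which conflicts with the add-on design in the Abstract and section 3.1

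*Protocol article*

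**What the plan says.** Three places in the protocol article define what each arm receives.

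- **Abstract.** "On the basis of symptomatic treatment drugs, the experimental group will additionally undertake acupuncture therapy 3 times a week for 4 weeks". This is an add-on design.
- **Section 3.1 (Experimental group).** It opens with a statement for both arms: "All subjects are able to use basic symptomatic treatment drugs, such as hypotensor, lipid-lowering drugs, hypoglycemic drugs, antiplatelet aggregation drugs, etc". It then gives the experimental arm its treatment: "On the basis of symptomatic treatment drugs, acupuncture will be performed". None of the three drugs for autonomic symptoms is named here.
- **Section 3.2 (Control group).** "On the basis of symptomatic treatment drugs, symptomatic treatment will be given for the following symptoms of autonomic nerve dysfunction". Three rules follow. The first reads "If the heart rate is greater than 100 beats/minutes, take propranolol tablets, and the dose is adjusted according to symptoms". The second gives clonazepam at an Ashworth grade of 3 or more in any limb. The third gives bromocriptine for a temperature above 38°C with sweating once infection is excluded. The section then prohibits other related treatment and says that concomitant medication is recorded at each visit.

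On outcomes, section 4.1 makes change in HRV primary. Section 4.2 makes change in CFS secondary and describes how severity is graded: "According to heart rate, respiration, blood pressure, body temperature, sweating and posture at the time of seizure". Table 1 schedules the CFS at baseline and week 4, and concomitant medication at baseline and weeks 1 to 4, without splitting by arm.

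**The concern.** In an add-on trial the two arms share the same drug treatment and differ only in the added component. Section 3.2 starts from the same base drugs as section 3.1 but then adds a second layer, and that layer appears under the control heading alone. The contrast actually set up is base drugs plus acupuncture against base drugs plus triggered autonomic drugs.

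This bears on both outcomes. The extra drugs are given expressly for symptoms of autonomic dysfunction, and the Introduction describes HRV as reflecting sympathetic and vagal activity. Heart rate, temperature and sweating are both triggers and CFS items, so the control CFS could change because a drug acted on one of its own items. Randomisation balances the patients; it does not balance a co-treatment that the protocol assigns to one arm.

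There is also a practical problem. Because section 3.2 prohibits related treatment beyond the symptomatic drugs, an investigator cannot tell from the text whether an acupuncture patient who meets a trigger may receive the drug.

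**Working it through.** **Step 1. Arms side by side, as written**

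| Component | Experimental | Control | Where |
|---|---|---|---|
| Base drugs (blood pressure, lipid, glucose, antiplatelet, open-ended list) | yes | yes | 3.1 |
| Acupuncture, 12 sessions | yes | no | Abstract, 3.1 |
| Propranolol on heart-rate trigger | not stated | yes | 3.2 |
| Clonazepam on muscle-tone trigger | not stated | yes | 3.2 |
| Bromocriptine on temperature and sweating trigger | not stated | yes | 3.2 |

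The arms differ in acupuncture and in the triggered drugs. The Abstract allows for the first difference only.

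**Step 2. Triggers against CFS items**

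- Heart rate: trigger and CFS item.
- Body temperature: trigger and CFS item.
- Sweating: part of a trigger and CFS item.
- Muscle tone (Ashworth): trigger, not a named CFS item.

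**Step 3. The plan's own sample size**

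Inputs from section 4.5: difference 531.0, SD 593.7, α = 0.05, β = 0.1. Section 4.6 makes tests two-sided.

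- Standardised difference: 531.0 / 593.7 = 0.894.
- Normal approximation: n = 2 × (1.960 + 1.282)² / 0.894² = 26.3, rounded up to 27 per arm. This reproduces the stated figure.
- With 10% non-response: 27 / 0.9 = 30 per arm, 60 in total. This also reproduces.
- Noncentral-t power at 27 per arm: 0.897.

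**Step 4. Illustration of the possible size**

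The documents give neither the share of controls who would meet a trigger nor the drug's effect on the index. Assume a share of 10–30% and an effect of 0.5–1.0 SD in those treated. Both ranges are assumptions.

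Shift in the contrast = share × effect:

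- low: 0.10 × 0.5 = 0.05 SD
- high: 0.30 × 1.0 = 0.30 SD

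Noncentral-t power at 27 per arm, two-sided 0.05:

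| Shift | Favours control | Favours experimental |
|---|---|---|
| none | 0.894 SD, power 0.897 | the same |
| 0.05 SD | 0.844 SD, power 0.861 | 0.944 SD, power 0.926 |
| 0.30 SD | 0.594 SD, power 0.573 | 1.194 SD, power 0.991 |

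If acupuncture had no effect, the shift alone would be declared a difference with probability 0.054 (0.05 SD) or 0.19 (0.30 SD), whichever its direction, against a nominal 0.05.

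**The case against.** The best defence is that the rules were meant for both arms and were put under the wrong heading. The list in section 3.1 is open-ended. The Introduction uses nearly the same term, symptomatic drugs, for the treatment of post-stroke autonomic dysfunction. The headings do not separate the arms cleanly either: a statement about all subjects sits under the experimental heading, and a general paragraph on concomitant medication sits under the control heading. This is plausible, and it means that an actual treatment imbalance is not established. But section 3.2 places the rules on top of the symptomatic drugs and names the control group alone, so the text needs correcting on this reading too.

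The distortion could also be negligible. Eligibility requires low HRV, not tachycardia, fever or raised tone, so few controls may ever meet a trigger. That stands as a limit on the size, not as an answer to the conflict.

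Four stronger readings are tempting and are not supported:

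- *The result could not be interpreted.* If the drugs are for control only, the trial compares two strategies on common background drugs. That can be interpreted, but it is not the comparison that the Abstract describes.
- *The triggers are not measured on schedule.* Table 1 puts the physical examination at baseline only ("Physical examination include height, weight, blood pressure and heart rate"), but the CFS covers heart rate, temperature and sweating in all patients at baseline and week 4. Only muscle tone has no scheduled row, and weekly vital-sign fields are detail that an article commonly leaves to the full protocol.
- *Use of the drugs goes unrecorded.* Concomitant medication is already scheduled through week 4 in both arms.
- *All three drugs act directly on the outcomes.* The documents show overlap with the CFS for three trigger signs. For HRV they support only the link through autonomic function; they do not state that heart rate determines HRV.

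**Conclusion.** The conflict is real and can be read directly from the Abstract, section 3.1 and section 3.2. Followed as written, the arms differ both in acupuncture and in drugs for autonomic symptoms, so the between-group difference in HRV and CFS would not estimate the effect of adding acupuncture.

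Neither the size nor the direction of the distortion can be fixed from the documents. The power range of 0.86 to 0.57 rests on an assumed trigger share, an assumed drug effect and an assumed direction favouring control. It shows what could happen and is not an estimate. The planned 27 per arm and 60 in total reproduce and are not affected. A reader might infer an established bias or a failure of randomisation; the documents show neither. What they show is a comparator described in two incompatible ways, which matters because it decides what the trial can conclude.

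**What to change.** The sponsor and investigators should reconcile the Abstract, section 3.1 and section 3.2. Which clinical rule should apply is theirs to decide and is not judged here.

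- If the symptom-triggered rules apply to both arms, move them out of section 3.2 into a section common to both groups.
- If they apply to control only, reword the Abstract, objective and conclusions as acupuncture versus symptom-triggered drug treatment, both on background drugs, and remove the add-on wording.

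In either case, report use of the three drugs by arm, from the concomitant medication record already scheduled in Table 1.

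The cost is protocol wording and one summary table from data already collected, with no change to the sample size or visits. The downside is that, under the second option, the trial supports a narrower claim.

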## 4. Outcomes

### 4.1. Primary outcome

The primary outcome measure is the HRV detection change, comprising 24-hour HRV detection and 60-minutes HRV detection compared with baseline (0 week) at week 4. 24-hour HRV detection comprises SDNN, SDANN, RMSSD, pNN50%, LF and HF. In addition, patients in the experimental group will be detected for 60 minutes at each time of treatment (from 10 minutes before the start of therapy to 30 minutes after the completion of treatment) to identify the change in LF and HF. The SDNN (the standard deviation of all NN intervals) represents the heart rate variability. SDANN (the standard deviation of the averages of NN intervals in all 5 minutes segments of the entire recording) and LF (power in low frequency range) represent the activity of both the sympathetic nervous system and the parasympathetic nervous system. RMSSD (the square root of the mean of the sum of the squares of differences between adjacent NN intervals), pNN50% (NN50 count divided by the total number of all NN intervals) and HF (power in the high frequency range) represent the activity of the parasympathetic nervous system.

During the HRV test, the patient should be in a supine resting posture to avoid tension, excitement, and deep breathing, and the surrounding environment should be kept calm. The test timing must be between 8 AM to 9 AM on the test day.

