### 4.5. Sample size

The study was a case-control study in a group design. Patients recovering from stroke with autonomic dysfunction were tested and compared using the HRV index. According to pre-experiment and literature, HRV index means *δ* = 531.0 and overall standard deviation *s* = 593.7, setting *α* = 0.05 and *β* = 0.1. PASS 11 program calculates *N*1 = *N*2 = 27 for experimental and control cases. We predicted 10% non-response. We plan to recruit 60 participants, 30 in each group.

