### 4.6. Statistical analysis

The design of the project was in line with a controlled study. According to the requirements of the standard operating procedures (SOP) for clinical research data management, the statisticians are conducted statistics independently, and are separated from the project research designers and operators. The test was designed by collecting information using the CRF scale. SPSS V.25.0 statistical software (IBM SPSS Statistics) will be used for analysis. The measurement data will be tested for normality and homogeneity of variance. For those with normal distribution were expressed as mean ± SD. The paired t-test will be used for comparison before and after treatment, and the 2 independent samples *t* test will be used for comparison between groups. If the variance is not uniform or does not conform to a normal distribution, the Wilcoxon rank- sum test will be used. The chi-square test will be used for counting data. Unless otherwise stated, hypothesis testing was carried out using 2-sided tests. The test level was *α* = 0.05, with *P* < .05 indicating a significant difference.

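### Six 24-hour HRV indices share the primary outcome with no lead index and no success rule, so the planned 5% error and 90% power, set for one unnamed index, do not describe it

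*Protocol article*

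**What the plan says.** Section 4.1 of the protocol article takes as its primary outcome the week-4 change in HRV from baseline, measured both over 24 hours and over 60 minutes. It then lists the 24-hour indices: "24-hour HRV detection comprises SDNN, SDANN, RMSSD, pNN50%, LF and HF". The abstract also speaks of primary outcomes in the plural. None of the six indices is put first.

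The 60-minute recording is a different kind of measurement. Section 4.1 says that "patients in the experimental group will be detected for 60 minutes at each time of treatment", and its purpose is "to identify the change in LF and HF". The text describes no such recording in the control group.

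Section 4.6 sets one rule for all comparisons: "The test level was *α* = 0.05, with *P* < .05 indicating a significant difference". On sidedness: "Unless otherwise stated, hypothesis testing was carried out using 2-sided tests". It gives no order of testing and no rule that combines the indices.

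Section 4.5 treats the outcome as one quantity: "Patients recovering from stroke with autonomic dysfunction were tested and compared using the HRV index". It uses a difference of 531.0 and a standard deviation of 593.7, with alpha 0.05 and beta 0.1. It gives neither the index nor the unit.

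**The concern.** A sample size based on one test at 0.05 fits a primary outcome with one test. Section 4.1 has six between-arm tests and no statement of what makes the trial positive. Two readings are open, and each breaks a different part of the plan:

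- **Any one index suffices.** The chance of a false-positive primary result exceeds 5%.
- **All six must be significant.** The error rate is protected, but power is below the planned 90%.

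Because the choice is left open, the headline index could be picked after the results are known. Choosing the primary endpoint and sizing the trial for it belong in the protocol, so this is not a detail that waits for an analysis plan.

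**Working it through.** **Inputs.** From section 4.1: six 24-hour indices. From section 4.6: two-sided 0.05 per test. From section 4.5: difference 531.0, SD 593.7, alpha 0.05, beta 0.1, 27 per arm, 10% non-response, 30 per arm recruited. Assumed, because the protocol gives none: a common pairwise correlation r between the six test statistics.

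**1. The plan's own figure.** n per arm = 2 × [(1.960 + 1.282) × 593.7 / 531.0]² = 26.27, rounded up to 27. Allowing for 10% non-response, 27 / 0.9 = 30. Both figures reproduce. Power at 27 per arm is 90.8% by the normal approximation and 89.7% by the exact t distribution. The calculation is right for one test.

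**2. False-positive rate if any one of six suffices, with no true effect.** If the tests are independent, 1 − 0.95⁶ = 26.5%. If they are correlated, the rate is P(at least one |Z| > 1.96) for six equally correlated normal statistics:

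| r | Rate | Multiple of 5% |
|---|---|---|
| 0 | 26.5% | 5.3 |
| 0.5 | 20.7% | 4.1 |
| 0.7 | 16.4% | 3.3 |
| 0.8 | 13.9% | 2.8 |
| 0.9 | 10.8% | 2.2 |

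An assumed block structure (SDNN with SDANN; RMSSD with pNN50% and HF; LF alone), with correlations of 0.8 to 0.9 within blocks and 0.3 to 0.7 between them, gives 14% to 19%.

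**3. Power if all six must be significant.** Suppose every index has the planned standardised effect, 531.0 / 593.7 = 0.894. Each statistic then has mean 0.894 × √(27/2) = 3.286. By the normal approximation, the chance that all six exceed 1.96 is about 70% at r = 0.5, 76% at 0.7, 79% at 0.8 and 83% at 0.9. If some indices have a smaller effect, it is lower.

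**4. What naming one index does.** There is one between-arm test at 0.05, so the error rate is 5%. The 27 per arm stands, provided that 531.0 and 593.7 describe the named index.

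**The case against.** **No success rule is written.** Section 4.6 says that P < .05 marks a significant difference in a comparison. It does not say that one such result makes the trial positive. A reader might infer the any-one rule and take the inflation as a fact of the plan, but the text does not support that. The inflation is conditional. The all-six reading has a cost of its own, so the gap remains.

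**The indices overlap.** Section 4.1 says that RMSSD, pNN50% and HF reflect the same parasympathetic activity. The independence figure of 26.5% is therefore an upper reference and not the expected value. This objection stands, and the verdict uses the correlated range.

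**The 60-minute indices.** A reader might count 60-minute LF and HF and reach eight tests (1 − 0.95⁸ = 33.7%). Those recordings are made in the experimental group only. They allow before-after comparisons within that arm, not a between-arm test, so they are not counted.

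**Sections 4.1 and 4.5 do not strictly contradict each other.** Sizing on one index while listing six is under-specification. That is a fair description, and it is enough for the point.

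**Adjustment may sit in an analysis plan that is not shown.** For that reason the absence of an adjustment is not, taken alone, the fault. The unnamed primary index is.

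**The discussion calls this a pilot trial.** Section 4.5 still plans a 90%-power test and section 4.6 still declares significance, so the label does not remove the need for a defined primary endpoint.

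**Conclusion.** The point holds. The 5% error and 90% power in the plan belong to one unnamed index and not to the six-index primary outcome of section 4.1. If any one index suffices, the between-arm false-positive rate is about 11% to 21% at assumed correlations of 0.9 to 0.5, roughly 2 to 4 times the stated level. If all six must be significant, power is about 70% to 83% at correlations of 0.5 to 0.9, given the planned effect on every index. The correlations are assumptions. The sample size arithmetic itself is correct.

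Two stronger inferences are not supported:

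- **That the size of 531.0 shows it must be LF or HF.** Section 4.5 gives no index or unit. The entry criteria in section 2.2 require LF below 300 ms² and HF below 200 ms², so a difference of 531.0 exceeds either ceiling. The figure should not steer the choice of endpoint.
- **That Bonferroni over six would cut the trial's power from 90% to 70%.** The 70% is power for one given index at 0.05/6. The chance that at least one index succeeds under Bonferroni is about 86% to 97% at correlations of 0.9 to 0.5, if all six share the planned effect. The case for a single index is clarity about what the trial tests, not that figure.

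**What to change.** - **Section 4.1:** name one 24-hour index as the single primary endpoint, compared between arms at two-sided 0.05. Section 2.2 puts the start of enrolment in November 2021, so this should be a dated amendment made without sight of outcome data.
- **Section 4.5:** state which index and unit 531.0 and 593.7 describe. If that is not the chosen index, restate the power for the chosen index at the planned size.
- **Sections 4.1 and 4.6:** move the other five 24-hour indices to secondary, either with Holm adjustment or labelled as supportive. Treat the 60-minute HRV as a within-arm descriptive outcome.

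The cost is a short amendment to three sections. Five indices can no longer be called primary, and the stated power may have to be revised if the sample size inputs turn out to describe a different index.

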Therefore, via the objective assessment of HRV detection and clinical feature scale (CFS) ratings, this research further highlighted the immediate impact of manual acupuncture on autonomic nerve dysfunction of varying severity in the convalescence period of stroke. Identify the cumulative impact of the immediate effect and establish that manual acupuncture has various effects on long-term repercussions of severe autonomic dysfunction in the convalescence period of stroke. In order to examine the feasibility and efficacy of acupuncture and moxibustion therapy on autonomic dysfunction in the convalescence period of stroke and to realize its practical value in clinical treatment.

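### The 60-minute HRV part of the primary outcome has no week-0 recording and no control-arm recording described, so its stated change from baseline and its between-group test cannot be obtained

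*Protocol article*

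**What the plan says.** Section 4.1 of the protocol article defines the primary outcome as the change in HRV, made up of "24-hour HRV detection and 60-minutes HRV detection compared with baseline (0 week) at week 4". The Abstract repeats this: "Primary outcomes include 24-hour HRV and 60-minute HRV detection at week 4 compared with baseline".

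Section 4.1 then explains how the shorter recording is made: "patients in the experimental group will be detected for 60 minutes at each time of treatment". Its purpose is to follow LF and HF, and its window runs "from 10 minutes before the start of therapy to 30 minutes after the completion of treatment". Section 3.1 gives the needling time: "The needles will be kept for 20 minutes after stimulating the acupuncture points".

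Table 1 in section 2.1 marks 24-hour HRV at baseline and week 4. It marks 60-minute HRV at weeks 1, 2, 3 and 4, with nothing at baseline. Section 3.2 describes drug treatment for the control group, during which "clinical observation was conducted for 1 month". It mentions no session and no 60-minute recording.

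Section 4.6 plans a paired t test for before versus after treatment and a two-sample t test between groups, with a Wilcoxon rank-sum test as the fallback.

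**The concern.** An outcome expressed as change from week 0 needs a week-0 value, and a randomised comparison needs values in both arms. For the 60-minute measure the article describes neither.

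This matters because the trial sets out to show an immediate effect of needling, and section 1 adds a further aim: "Identify the cumulative impact of the immediate effect". The 60-minute recording is the only measurement taken around a session, so the immediate effect rests on it. A shift in LF or HF within a session, in patients asked to lie calmly for the test, could come from the needles or from the rest. If that shift keeps its primary label, a significant within-arm result could be reported as a positive primary finding of a randomised trial, although randomisation played no part in it.

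**Working it through.** **Step 1. The plan's own sample size (section 4.5).** Inputs: difference 531.0, SD 593.7, two-sided alpha 0.05, power 90%.

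- Standardised difference: 531.0 / 593.7 = 0.894.
- n per group = 2 × (1.960 + 1.282)² × (593.7 / 531.0)² = 2 × 10.51 × 1.250 = 26.3, rounded up to 27. This matches the stated 27. An exact t calculation gives 27.27, that is 28, and 27 per group has power 89.7%.
- With 10% non-response: 27 / 0.90 = 30 per group, 60 in total. This also matches.

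The figure is sound for a comparison of two groups, so it presupposes an outcome observed in both. Section 4.5 does not say which HRV index it refers to.

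**Step 2. What the 60-minute window is.** 10 minutes before + 20 minutes of needle retention + 30 minutes after = 60 minutes. The recording is built around an acupuncture session, and controls have no such session.

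**Step 3. Required against scheduled.**

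| Component | Week 0 | Week 4 | Control arm |
|---|---|---|---|
| 24-hour HRV | marked | marked | not excluded anywhere |
| 60-minute HRV, as the primary definition requires | needed | needed | needed for the between-group test |
| 60-minute HRV, as scheduled | not marked | marked | none described |

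The empty week-0 cell does not look like an extraction fault. The 60-minute row carries four marks, in the same columns as the two intervention rows, while the concomitant-medication and adverse-reaction rows carry five, starting at baseline.

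**Step 4. Count of data.** Acupuncture arm: up to 30 × 12 = 360 session recordings, all in weeks 1 to 4. Week-0 recordings: 0 in either arm. Control recordings described: 0 of 30 patients.

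**Step 5. What can be computed.** In the acupuncture arm one can compute a post-minus-pre change within each session, or a change from the 10-minute segment before the first needling to a later session. Both are uncontrolled, and neither is the stated week-0 to week-4 change.

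**The case against.** **It may be meant as a side measure.** Section 4.1 introduces the session recordings as an addition to the 24-hour ones. But the sentence that defines the primary outcome, and the Abstract, both name the 60-minute measure. If a side measure was intended, the text needs the correction proposed here.

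**Table 1 is not split by arm.** True. The restriction to one arm rests on section 4.1, and section 3.2 agrees with it. The missing baseline mark does not depend on that restriction.

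**The first pre-needling segment could serve as baseline.** It is a pre-treatment value, so a reader who infers that no change of any kind can be computed goes too far. But the definition names week 0, Table 1 puts the first session in week 1, and there would still be no control.

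**The full protocol or analysis plan may settle it.** That would excuse an omission. Here the article contradicts itself on what is measured, in whom and when.

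**Stronger readings that the article does not support.** A reader might infer that the trial has no randomised HRV comparison. It has one: 24-hour HRV is scheduled at weeks 0 and 4 with no restriction by arm. A reader might also infer a specific inflation of the type I error, from testing each of 12 sessions or from pooling all sessions as independent. The article plans neither. Section 4.6 speaks of before and after treatment, which most naturally means the four-week course, and the handling of repeated sessions may properly sit in an analysis plan that is not shown.

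**Conclusion.** Wrong as written. The Abstract and section 4.1 define a primary component that the schedule cannot deliver: 0 week-0 recordings in either arm and no recording described for any of the 30 controls. The stated change and the between-group test are therefore unavailable for 60-minute HRV. The acupuncture-arm change that remains cannot separate needling from quiet rest.

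The conclusion rests on taking section 4.1 at its word about the arm and Table 1 at its word about timing. It needs no assumed variance or correlation. It does not reach the 24-hour component, and the sample size reproduces.

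**What to change.** Reconcile the Abstract, Table 1 and section 4.1:

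- Keep 24-hour HRV, in both arms at weeks 0 and 4, as the primary outcome. Remove 60-minute HRV from the primary outcome in the Abstract and section 4.1.
- Define 60-minute HRV as a non-primary measure in the acupuncture arm only: the change in LF and HF from the 10-minute pre-needling segment to the post-needling segment of the same session. Delete the week-0 comparison for it, and mark the Table 1 row as experimental group only.
- State that it supports no between-group or efficacy conclusion.
- Make the patient the unit of analysis. One option is a one-sample test on each patient's mean session change. Another is a mixed model with a patient-level random phase effect as well as a random intercept. A random intercept alone is not enough: it enters the pre and post segments alike and cancels from their difference, so variation between patients in the response stays unmodelled.
- Do not present a phase-by-session interaction as the test of the cumulative aim. It tests whether the within-session response grows. The Discussion describes early effects building into long-term benefit, which could show as a rising pre-needling level with no interaction at all.

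This costs wording and a simple analysis, with no new patients or procedures. The downside is that the immediate-effect result becomes descriptive. If the sponsor wants a controlled immediate effect, matched 60-minute rest recordings in the control arm would be needed, which is extra work.
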